## Abstract

**Background:**

Mental Health First Aid (MHFA) is a mental health intervention that teaches people how to identify, understand and help someone who may be experiencing a mental health issue. Reviews of the implementation of MHFA found between 68 and 88% of trained Mental Health First Aiders had used their skills when in contact with someone experiencing mental health difficulties. Reviews evaluating the impact of MHFA suggest positive outcomes. However, to date, there has been no systematic, rigorous evaluation of the impact of MHFA on recipients of the intervention, the organisations providing it and the cost-effectiveness of MHFA overall. This trial will evaluate the effectiveness and cost-effectiveness of MHFA.

**Methods:**

The study is a multi-centred, two-arm clustered randomised controlled trial. Organisations will be randomly allocated to the control or intervention (estimated sample size 800 recipients). The intervention is the standard MHFA intervention provided by Mental Health First Aid England (MHFAE). The control condition will be organisations having a brief consultation from MHFAE on promoting mental health and well-being in the workplace. The primary outcome is health seeking behaviour, measured using the Actual Help Seeking Questionnaire, at 6 months’ follow-up. Data collection will be undertaken at baseline (T0), post-intervention—up to 3 months (T1), at 6 months (T2), 12 months (T3) and 24 months (T4). The primary analysis will be conducted on those participants who receive MHFA, a per protocol analysis.

**Discussion:**

The study is the first to evaluate the effect of MHFA in the workplace on employees with direct and indirect experience of the intervention, when compared with usual practice. Being also the first to assess, systematically, the social impact of MHFA and investigate its cost-effectiveness adds to the originality of the study. The study promises to yield important data, as yet unknown, regarding the effectiveness, cost-effectiveness, implementation issues, and the sustainability of MHFA in the workplace.

**Trial registration:**

Clinicaltrials.govNCT04311203. Registered on 17 March 2020.

## Introduction

### Background and rationale {6a}

Mental Health First Aid (MHFA) is a mental health intervention on how to identify, understand and help someone who may be experiencing a mental health issue. It is designed to help Mental Health First-Aiders to listen, reassure and respond, even in a crisis—and potentially stop a crisis from happening. MHFA courses were developed in 2000 to equip trainees with first-aid skills to support people with mental health problems [1]. MHFA training is reported to increase trainees’ knowledge, confidence and skills in identifying mental health problems, as well as reducing negative attitudes and stigma [1–4].

Reviews of the implementation of MHFA found between 68 and 88% of trained mental health first aiders had used their skills when in contact with someone experiencing mental health difficulties [5–7]. Mental health interventions in the workplace have been linked to increased productivity, reduced levels of absenteeism and significant economic gains [8].

Recently, a large study (MENTOR) [9] investigated the implementation, use and utility of MHFA in the workplace using multiple research methods and reported that MHFA was useful for raising awareness of mental health in the workplace, but stated it may not be the best or only means of doing so and may not necessarily be the most cost-effective. The MENTOR study highlighted implementation issues relating to lack of clarity around the role of the mental health first aider and potential safety concerns, leading them to recommend further research and evaluation of the intervention. Implementation challenges such as role conflict relating to a person carrying out the first aider role versus other roles and responsibilities they may have within the organisation have been identified previously [10]. Handling the potentially hierarchical relationship between the mental health first aider and recipient, who may be a subordinate, is one such example of this potential role conflict [10].

Since the original research on MHFA, in 2001, there have been numerous studies evaluating MHFA among various populations, with benefits evident in adults and young people, across diverse organisations. However, there is limited evidence from studies conducted outside Australia, where the research was first conducted. Little evidence has shed light on the challenge of implementing MHFA in a range of organisations, and there is no evidence establishing the cost-effectiveness of MHFA, especially when compared to other ways of providing mental health and well-being support in the workplace. Few studies test the effect of MHFA directly on recipients. In addition, no empirical studies have directly investigated its wider social impact. MHFA appears to reduce mental health stigma in the workplace [1, 2, 9], and the potential of MHFA to reduce stigma and lower sickness absence and presenteeism in the workplace [8] speaks to wider social benefits such as keeping people in work and reducing discrimination. However, the lack of a social impact assessment of MHFA remains a significant gap in the evidence base.

In sum, evidence suggests MHFA benefits’ organisations by giving employees the tools to keep themselves and their colleagues healthy and facilitating a long-term cultural change across organisations. However, there has been no systematic investigation of the impact of MHFA on recipients of the intervention, the organisations that provide MHFA and the cost-effectiveness of MHFA. Furthermore, the wider societal impact of MHFA is not evident from the empirical literature.

### Objectives {7}

The EMPOWER study will implement a cluster randomised controlled trial (RCT) to examine the effectiveness and cost-effectiveness of MHFA in the workplace on help-seeking behaviours of employees, with embedded qualitative, process and social impact evaluations. In order to best answer questions regarding effectiveness, mechanisms and acceptability/feasibility, a design combining a RCT with a qualitative component will be adopted. The qualitative component will assess the efficiency, utility, usability, feasibility, acceptability and the mechanisms underlying the intervention. This protocol describes the trial element of EMPOWER.

### Trial design {8}

The study is a multi-centred two-arm cluster RCT comparing organisations implementing MHFA (intervention arm) with a consultation on mental health and wellbeing in the workplace (control arm).

## Methods: participants, interventions and outcomes

### Study setting {9}

Data will be collected from employees working in eligible UK organisations expressing an interest to MHFAE in undertaking MHFA training.

### Eligibility criteria {10}

Inclusion criteria are as follows: organisations expressing an interest (directly to MHFAE) in undertaking MHFA training, who have not undertaken this training previously and who agree to participate and are able to provide data on sickness absenteeism, presenteeism and other productivity data. For the purposes of this study, participants will be all employees working in each organisation who provide help-seeking outcome data.

Exclusion criteria are as follows: organisations who have already introduced MHFA across all sites and departments; those who decline to participate in adopting MHFA training; and organisations, employees, mental health first-aiders and recipients who participated in the pilot study.

The intervention will be delivered by qualified MHFAE trainers.

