### Who will take informed consent? {26a}

The research team will elicit written agreement to participate from a relevant Senior Manager in each organisation. All employees within each included organisation will be invited to participate and be provided with a participant information sheet (PIS) providing detailed information and procedures regarding the study. The information provided will include the following: the benefits and potential harm of participation; how the team will collect, store and process data; and the participant’s right to withdraw from the study at any time, at least 2 weeks prior to any outcome assessment. Participant consent will be sought, using Qualtrics, before completing the online survey.

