### Outcomes {12}

#### Primary outcome

The primary outcome is Employees’ help-seeking behaviour at 6 months measured by the Actual Help-Seeking Questionnaire [AHSQ] [11]. The AHSQ measures help-seeking behaviour in the 2 weeks preceding the assessment and will be assessed at baseline, 6, 12 and 24 months. Help-seeking behaviour is determined by listing the number of help sources, the type of help sought and whether help seeking has occurred during the allocated time period.

The primary analysis will be conducted on those participants who receive MHFA and therefore is a per protocol analysis. Further analyses will examine the impact of the intervention at the organisational level using an intention-to-treat analysis with all respondents included.

As this is a small non-random subsample of randomised participants, it is recognised that this analysis will be vulnerable to selection bias and uncontrolled confounding. For this reason, a range of baseline participant characteristics will be included in the primary analysis to mitigate these limitations.

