#### Recruitment {15}

Organisations expressing an interest (directly to MHFAE) in undertaking MHFA training, who are willing to take part in the study, will be asked to contact [name] (GD: Centre for Mental Health) for detailed information about the study. Then, if willing to take part, the Senior Manager will sign a written agreement and their contact details will be sent to the research team. The research team will email the Senior Manager, detailing what will happen next, asking for company demographics (see secondary outcomes below) and requesting they send a standard email to ALL employees providing information about the study with a link to the survey for completion of baseline measures. One, 2 and 3 weeks later, the research team will send the Senior Manager another standard email, to be sent to ALL employees, as a gentle reminder to complete the survey.

At each follow-up, the research team will send participants (Senior Managers) up to four weekly email reminders to remind employees to complete measures.

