**Assignment of interventions: allocation**

**Sequence generation {16a}**

**Concealment mechanism {16b}**

**Implementation {16c}**

#### Randomisation

The unit of randomisation is organisation, and randomisation of organisations will be stratified by size of organisation, with three strata being defined [22], small (< 50 employees), medium (50–249 employees) and large (> 250 employees). The randomisation schedule will be generated by GD using Random.org (https://www.random.org/randomness/) and allocation assigned to an organisation after completion of baseline measures.

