### Data collection and management

#### Plans for assessment and collection of outcomes {18a}

Consent, baseline and follow-up data will be collected online, with the option for employees to complete them in hard copy should they be unable to complete them online. The research team will email the designated contact from each organisation, giving instructions and information for them to send to ALL employees and a link to the survey. One, 2 and 3 weeks later, follow-up emails will be sent to the same contact, asking them to send a reminder email, with a repeat survey link. After this period, participants who have not completed the survey will be treated as lost to follow-up.

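### The participant definition and the ITT set are not closed at allocation, so employees who first respond after their organisation's arm is known can enter the ITT comparison

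*Protocol article*

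**What the plan says.** All references are to the protocol article.

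- **Who is a participant.** Eligibility criteria {10}: "participants will be all employees working in each organisation who provide help-seeking outcome data".
- **Who is in the ITT set.** Primary outcome: the organisational-level comparison is made "using an intention-to-treat analysis with all respondents included". The primary analysis itself is per protocol, in those who receive MHFA.
- **When consent is taken.** Who will take informed consent? {26a}: "Participant consent will be sought, using Qualtrics, before completing the online survey". This is not limited to the baseline survey.
- **How surveys are sent.** Plans for assessment and collection of outcomes {18a} opens with "Consent, baseline and follow-up data will be collected online". It then says that the organisation's contact is emailed, "giving instructions and information for them to send to ALL employees and a link to the survey".
- **Follow-up reminders.** Recruitment {15}: "At each follow-up, the research team will send participants (Senior Managers) up to four weekly email reminders to remind employees to complete measures".
- **When allocation occurs.** Randomisation: "allocation assigned to an organisation after completion of baseline measures".
- **Blinding.** Who will be blinded {17a}: participants know their allocation.

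Other parts read as if a cohort is enrolled at baseline and followed. Sample size {14} allows 15% attrition at 6 months. Section {18a} treats participants who do not complete the survey as lost to follow-up. Statistical methods {20a} estimates the effect from an interaction between time (baseline versus 6 months) and arm.

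**The concern.** Allocating an organisation after its baseline survey guards against recruitment bias in a cluster trial, but only for people who entered by then. If staff can also enter later, they decide whether to respond while knowing what their employer was allocated. An employee who has had contact with a mental health first aider may have a reason to answer a help-seeking survey for the first time at 6 months. A control employee has no equivalent prompt. The arms could then differ in who answers, and not only in what MHFA does.

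This matters most for the ITT analysis. The Primary outcome section accepts that the per-protocol primary analysis is open to selection bias and confounding. The ITT comparison is therefore the one that randomisation could protect, and that protection depends on its membership being settled before allocation.

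**Working it through.** **1. The stated rules side by side.** Take an employee who ignores the baseline survey and first answers at 6 months.

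| Rule | Requirement | Met? |
|---|---|---|
| Participant ({10}) | Employee who gives help-seeking outcome data | Yes |
| Consent ({26a}) | Given online before the survey | Yes, at 6 months |
| Survey link ({18a}) | Sent to all employees; the section covers follow-up data | Nothing excludes this employee |
| ITT set (Primary outcome) | All respondents | Yes |
| Allocation (Randomisation) | Follows baseline | Already made, and not blinded ({17a}) |

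No sentence requires consent or a completed baseline before allocation. Late entry is left open; it is not expressly permitted.

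**2. The plan's own sample size.** Inputs from Sample size {14}: means 1 and 3, SD 8, alpha 0.05 (taken as two-sided), power 80%, attrition 15%, cluster size 29, ICC 0.01.

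- Standardised difference: 2/8 = 0.25. A two-sample t-test needs 253 per arm, so 2 × 253 = 506.
- Attrition: 506/(1 − 0.15) = 595.3, so 596.
- Design effect: 1 + (29 − 1) × 0.01 = 1.28. Then 596 × 1.28 = 762.9, so 763.

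All three stated figures reproduce. The attrition step describes a group fixed at baseline that shrinks by 6 months. A set that can also gain members after allocation is a different population.

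**3. Illustration of what late entry could do.** From {14}: 72 employees and 40% response give 28.8, or about 29 responders, so 72 − 29 = 43 do not respond at baseline. With 15% attrition, 29 × 0.85 = 24.65 responders remain at 6 months.

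Assumed, not in the documents: a fraction f of the 43 join in MHFA organisations; they average 3 sources against 1 for others (a gap of 2); there is no matching shift in control; and all joiners stay in the analysis.

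With joiners j = f × 43, the shift in the MHFA mean is 2j/(24.65 + j).

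| f | j | Shift (sources) | Share of the planned difference of 2 |
|---|---|---|---|
| 5% | 2.15 | 4.3/26.80 = 0.16 | 8% |
| 10% | 4.30 | 8.6/28.95 = 0.30 | 15% |
| 20% | 8.60 | 17.2/33.25 = 0.52 | 26% |

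**4. Would the model remove late entrants?** Table 1 schedules demographics at baseline only, and {20a} and {20b} put demographic covariates in the primary model. A late entrant would lack them on the stated schedule and would drop out unless they were imputed or collected later. However, the Primary outcome section does not say that the ITT analysis uses the same covariates. A mixed model without them can use a record that exists only at 6 months.

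**The case against.** The strongest reply is that the plan intends a closed cohort and that the article merely condenses it. Attrition, loss to follow-up and the interaction all point that way. Detailed analysis sets commonly sit in the full protocol or SAP, and missing covariates may exclude late entrants anyway. This stands in part: late entry is an opening in the text and not a stated intention. But the article does state who is a participant and who is in the ITT set, and those rules depend on responding. Exclusion through missing covariates would be accidental and would conflict with including all respondents.

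It is also fair that the ITT is a further analysis and not the primary one, which limits the reach of the point.

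A reader might infer more than the documents support:

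- *That a baseline responder who later stays silent ceases to be a participant.* The AHSQ is assessed at baseline, so this person has given help-seeking outcome data and meets the definition; {18a} counts such people as lost to follow-up.
- *That managers send every follow-up link to all staff, with effort differing by arm.* Recruitment {15} speaks of all employees for baseline and, at follow-up, only of reminders. Section {18a} does not say that its procedure repeats at each wave. Differing effort is conjecture.
- *That the retention section {18b} contradicts {15} and {18a} on reminders.* It does not say who sends them, so there is no conflict.
- *That 8% to 26% estimates the bias.* Every driver is assumed, and the gap of 2 borrows the trial's own target. If late entrants sought more help because of MHFA, part of the shift would also be a real effect in a selected group.

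**Conclusion.** The point holds as a defect in how the analysis population is defined. As written, employees who first respond after unblinded allocation can enter the ITT set, and this is inconsistent with the closed cohort assumed in the sample size, the follow-up rule and the effect estimate. The conclusion rests on reading {18a} as covering follow-up as well as baseline, which its opening sentence supports, and on the absence of any sentence closing the cohort.

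The size of any bias is unknown. The shift of 0.16 to 0.52 sources shows only that modest selective entry need not be negligible against a target of 2, and it presumes that late entrants remain in the model. No stated figure needs to change. The correction is worth making because it is specific, cheap and bears on the comparison that randomisation is meant to protect.

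**What to change.** In Eligibility criteria {10} and Primary outcome, define participants and the ITT set as employees who consented and completed the baseline AHSQ before their organisation was allocated. Analyse them as allocated, whatever their later contact with MHFA and whether or not they respond at follow-up. Report anyone who first responds after allocation only in a labelled sensitivity analysis.

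This is a wording change and fits the repeated-measures design already planned. Its cost is the loss of late entrants' responses from the main ITT analysis. The survey procedure can stay as it is: collecting email addresses so that the research team contacts employees directly is not needed for this correction, and would be a debatable addition while recruitment is under way.

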### Who will take informed consent? {26a}

The research team will elicit written agreement to participate from a relevant Senior Manager in each organisation. All employees within each included organisation will be invited to participate and be provided with a participant information sheet (PIS) providing detailed information and procedures regarding the study. The information provided will include the following: the benefits and potential harm of participation; how the team will collect, store and process data; and the participant’s right to withdraw from the study at any time, at least 2 weeks prior to any outcome assessment. Participant consent will be sought, using Qualtrics, before completing the online survey.

### Additional consent provisions for collection and use of participant data and biological specimens {26b}

N/A

### Interventions

#### Explanation for the choice of comparators {6b}

The control arm is termed as usual practice and is defined as an organisation that has not previously introduced MHFA and agrees to not introduce the 2-day MHFA training during the period of the study. The organisations allocated to usual practice arm will receive a brief consultation from MHFAE on the promotion of mental health and wellbeing in the workplace.

#### Intervention description {11a}

The MHFA intervention has three parts:
The 2-day MHFA training provided by MHFAE. This is a manualised training programme designed to provide individuals with the following: an in-depth understanding of mental health and the factors that can affect wellbeing, practical skills to spot the triggers and signs of mental health issues, confidence to step in, reassure and support a person in distress, enhanced interpersonal skills such as non-judgemental listening, knowledge to help someone recover their health by guiding them to further support—whether that is self-help resources, through their employer, the NHS, or a combination.Raising awareness of the presence of MHFA in the organisation.The application of MHFA to participants in the workplace. The MHFA training uses a manualised five-stage approach, ALGEE: Approach the person, assess and assist with any crisis; Listen and communicate non-judgementally; Give support and information; Encourage the person to get appropriate professional help and Encourage them to seek other forms of support.

MHFAE recommend training one employee in MHFA per ten employees; however, organisations are free to ask for any number of employees to be trained. The current study will record the ratio of participants trained in each organisation. No stipulation is made as to the selection of participants to be trained, and organisations are encouraged to advertise the training to all staff. The selection criteria used by each organisation will be assessed in the qualitative component of this study.

#### Criteria for discontinuing or modifying allocated interventions {11b}

A Trial Steering Committee (TSC), which will audit the conduct of the study, will have ultimate responsibility for deciding if the trial should be stopped on grounds of safety or efficacy. The occurrence of serious adverse events to participants will be assessed by the TSC and may be grounds for discontinuing the trial.

#### Strategies to improve adherence to interventions {11c}

A sample of MHFA training, staggered throughout the trial, will be observed by two independent researchers using structured observation forms to assess variability in fidelity between instructors, sites, and over time. This will ensure all interventions are being delivered as per protocol, to equally high standards, to improve participant adherence.

